### 8.3 Other study parameters

For the economic analysis see also the description above (section 6.3). Here we will use a mixed repeated measures design. Missing values will be interpolated between the available assessments.

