**Study procedure:**

Visit 1 (Inclusion and genotyping): All eligible patients will be asked to provide written informed consent. Inclusion and exclusion criteria are checked and baseline and demographic variables will be collected (complete somatic and psychiatric history, physical examination, inventory of medication and use of drugs, and laboratory studies equivalent to the procedures in standard clinical care).

Genotyping: For eligible patients relevant genetic variants in *CYP2D6* and *CYP2C19* will be determined. These variants explain in 90-95% of the cases with changes in *CYP2D6* and *CYP2C19* enzyme activity.

Based on the drug choice and based on the latest allele definition tables (KNMP kennisbank achtergrondteksten) each patient will be classified into a metabolic phenotype category (PM,IM,EM or UM).

The time period between visits 1 and 2 will be used for washout of psychiatric drugs to which insufficient response occurred and/or that interfere with study medication (also in accordance to standard clinical procedures). Genotype information and the consequent drug dosing advice will be available within five working days after visit 1.

Visit 2: Baseline (start TCA therapy). Completion of baseline assessments of secondary clinical outcome measures. During this visit TCA treatment will be started according to the instructions per treatment strategy group (genotype guided dosing vs. dosing as usual). TCAs will be initially prescribed once daily in the evening, although the dosing regimen can later on be altered according to the patient preference. The TCAs will be prescribed and delivered by either the in-hospital or outpatient pharmacy, dependent on the situation of the patient.

Visits 3 to 9 treatment phase: During seven weeks the patients receive TCA treatment based on the dosing instructions as described above (Strategies 1 and 2). Patient assessments will take place weekly for (a) TCA concentration measurements if indicated (see description) (b) the secondary clinical outcome measures as described under visit 1 (side effects and depressive symptoms). Adherence to drug treatment will be checked weekly either by review of a drug diary kept by the patient or by interviewing the patient during visits.

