#### ECONOMIC EVALUATION (COST EFFECTIVENESS).

We aim to prospectively study cost effectiveness of the intervention during 26 weeks. This period is longer than the 7 weeks of the clinical trial, because we assume that important positive effects on patient important outcomes (quality of life and cost savings) can also be expected beyond this period.

The impact of the intervention on the quality of life of patients will be assessed both by the EuroQol 5 dimensions with 5 levels (EQ5D5L) and the SF36 at weeks 0, 2, 4, 6, 13 and 26 following randomization. Primarily, utility will be derived from the EQ5D5L as recommended by the Dutch guidelines for cost-effectiveness study. However, because SF36 seems to be more valid for this particular patient population because it includes more items within the mental health domain, utility will also be derived using the SF36 system as a secondary analysis. The derived utility will be used to estimate a Quality adjusted life year (QALY) according to the trapezium rule.

The cost analysis consists of two main parts. First, at patient level, volumes of care related to MDD and TCA therapy will be measured by means of the iMTA Medical Consumption Questionnaire. This questionnaire measures all relevant health care related costs like outpatient visits at any medical specialist and hospitalizations. In addition the medication use will be derived from the electronic patient records. Loss of productivity due to illness or recovery, will be estimated based on patient reported absences from paid (or unpaid) labor measured with the Productivity Cost Questionnaire. The iMTA Medical Consumption Questionnaire and the Productivity Cost Questionnaire will be administered at the start of the study (day 0) at week 13 and at week 26.

The second part of the cost analysis consists of determining the cost prices for each volume of consumption. The standard cost prices from the 'Dutch Guidelines for Cost Analyses' and [www.medicijnkosten.nl](http://www.medicijnkosten.nl) will be used. For units of care where no standard prices are available real costs prices will be determined on the basis of full cost pricing. Productivity losses will be

valued by means of the friction cost method. In the end volumes of care will be multiplied with the cost prices for each volume of care to calculate costs.

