**6.6 Follow-up of subjects withdrawn from treatment**

The data of withdrawn patients will be included in the analyses based on the intention-to-treat model. If possible we will keep withdrawn patients in the study for the part of the economic evaluations.

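### The only stated rule for missing economic data, interpolation, cannot fill follow-up lost before week 26, and it fills a lone missing week-13 cost half from the pre-treatment baseline

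*Protocol*

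**What the plan says.** Protocol section 8.3 covers the statistical handling of the economic data in two sentences after a cross-reference: "Here we will use a mixed repeated measures design", and then "Missing values will be interpolated between the available assessments". It gives no separate rule for costs and utilities, and none for values missing after a patient's last assessment.

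The schedule is in the economic evaluation part of section 6.3. The horizon is stated as "We aim to prospectively study cost effectiveness of the intervention during 26 weeks". Utilities (EQ5D5L, and SF36 as a secondary source) are collected "at weeks 0, 2, 4, 6, 13 and 26 following randomization", and "The derived utility will be used to estimate a Quality adjusted life year (QALY) according to the trapezium rule". The medical consumption and productivity questionnaires "will be administered at the start of the study (day 0) at week 13 and at week 26". Medication use is taken from electronic patient records instead.

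Day 0 is described under the study procedure as "Visit 2: Baseline (start TCA therapy"), so resource use reported at that visit precedes TCA treatment. On withdrawal, section 6.6 keeps withdrawn patients' data in the intention-to-treat analyses and adds: "If possible we will keep withdrawn patients in the study for the part of the economic evaluations".

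**The concern.** Interpolation bridges a gap between two observed values. In a trial with 26 weeks of follow-up and a 7-week treatment phase, the more usual gap has nothing after it: the patient stops returning questionnaires. The protocol foresees this, because follow-up of withdrawn patients is conditional. Its withdrawal criteria (section 6.4.1) include urgent need for a different biological treatment and intolerable adverse reactions. Both are related to response and side effects, on which the arms are expected to differ. The one rule that is fixed does not reach these patients.

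For costs there is a second problem. With only three questionnaires, the sole point that can be interpolated is week 13, and its left-hand neighbour is the pre-treatment baseline.

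The comparison of costs is a stated secondary objective. Its results feed the cost-utility ratio, the 5000 simulations, the willingness-to-pay curves and the budget impact analysis.

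**Working it through.** The protocol gives no missing-data rate and no sample size for the economic analysis, so there is no stated figure to reproduce. The inputs are the two assessment schedules in section 6.3. Missing rates and cost ratios below are assumptions, shown as ranges.

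**1. Loss to follow-up and the QALY**

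The utility assessments at weeks 0, 2, 4, 6, 13 and 26 give trapezium intervals of 2, 2, 2, 7 and 13 weeks (total 26).

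- Lost after week 13: the last interval has no end value, 13/26 = 50% of the horizon.
- Lost after week 6: the last two intervals have none, (7 + 13)/26 = 20/26 = 77%.

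Week 26 closes both the utility and the cost schedule, so a missing week-26 value can never be interpolated. By contrast, a lone missing week-13 utility can be filled from weeks 6 and 26. The weights are (26 − 13)/20 = 0.65 on week 6 and (13 − 6)/20 = 0.35 on week 26, and no baseline value is involved.

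**2. A lone missing week-13 cost questionnaire**

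Costs are observed at weeks 0, 13 and 26. The interpolation weights for week 13 are (26 − 13)/26 = 0.5 on day 0 and 13/26 = 0.5 on week 26:

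filled week-13 cost = 0.5 × day 0 + 0.5 × week 26.

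Assume that the week-13 and week-26 questionnaires each cover a 13-week period with true cost 1, and that the day-0 questionnaire gives a cost r. The filled value is 0.5r + 0.5 and the patient's 26-week total is 1.5 + 0.5r, against a true total of 2. The relative error is (r − 1)/4.

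| Day-0 cost relative to a trial period (r) | Filled week-13 cost | 26-week total | Error |
|---|---|---|---|
| 0.5 | 0.75 | 1.75 | −12.5% |
| 1.5 | 1.25 | 2.25 | +12.5% |
| 2 | 1.50 | 2.50 | +25% |
| 3 | 2.00 | 3.00 | +50% |

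These are errors for an affected patient, not for the arm mean.

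**3. Effect on the arm comparison at week 13**

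Assume no arm difference at day 0 and a constant difference d at weeks 13 and 26. In patients whose week-13 cost is filled, the expected difference is 0.5 × 0 + 0.5 × d = d/2. With a fraction m filled in each arm, unrelated to cost:

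expected difference = (1 − m)d + m(d/2) = d(1 − m/2).

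- m = 10%: 5% dilution
- m = 20%: 10% dilution
- m = 30%: 15% dilution

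If the 26-week cost is the sum of the two periods and all week-26 values are present, the difference in the total is d(1 − m/2) + d = 2d(1 − m/4). The dilution of the total is then half as large: 2.5%, 5% and 7.5%.

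**The case against.** **Dropouts may not be excluded.** A reader might infer that patients lost after week 6 fall out of the analysis and that the result rests on completers. The documents do not support this. No complete-case rule is stated. The repeated-measures model in section 8.3 could, if fitted by likelihood, retain incomplete records. Sections 6.6 and 8 place the analyses under intention-to-treat. The decision model takes costs and utilities as distributions and does not require a complete QALY from every patient. What stands is narrower: the only stated fill rule leaves these gaps open.

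**Uncertainty may not be too narrow.** A reader might also infer that filled values, counted as observed, make the standard errors materially too small. The protocol does not say how filled values enter the variance, and the effect looks small. A simulation used 100 per arm, correlations of 0.3 to 0.7 between time points and 20% missing at week 13. The unadjusted standard error was 0.136 to 0.140, against 0.141 with complete data, which is 1 to 4% lower. It roughly matched the actual spread of the estimates (0.139 to 0.141). It was 12 to 14% below the standard error from observed cases only (0.158), but that does not show material understatement.

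**The cost problem is confined.** It needs week 13 missing and week 26 present. It concerns questionnaire costs only; medication use comes from records and may be unaffected. The questionnaires' recall period is not stated, so the exact span of pre-treatment care reported at day 0 is unknown. All of this is correct and limits the size of the problem.

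**Could this be left to the SAP?** Missing-data detail often is. Here, however, the protocol itself fixes a rule, and that rule does not suit the schedule.

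**Conclusion.** The point holds in limited form. On the protocol's own schedules, interpolation can never supply week 26. It leaves 50% of the QALY horizon without an end value after loss beyond week 13, and 77% after loss beyond week 6. These shares are exact; how many patients they apply to is not given.

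Where only the week-13 cost questionnaire is missing, half of the filled value comes from the pre-treatment baseline. The resulting dilution of the week-13 cost difference, about 10% at 20% missing, depends on the assumed missing rate, on equal arms at baseline and on a constant difference afterwards. The direction and size of the error in a patient's total depend on how baseline costs compare with trial costs, which the documents do not state.

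The rule is also unnecessary beside the model named with it. The primary endpoint and the HAM-D and side-effect analyses are untouched. This is a correction that should be made to a secondary economic analysis.

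**What to change.** Delete the interpolation sentence in section 8.3 and replace it with one of two methods.

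1. A likelihood-based mixed model for repeated measures on the observed utilities and costs, with no prior filling. The trapezium rule is linear, so mean QALYs per arm can be computed from the fitted visit means.
2. Multiple imputation by arm of utilities and costs at each time point. Use as predictors the weekly depression and side-effect scores and the stratification factors (phenotype, drug, inpatient or outpatient status), all already collected. Carry the imputation uncertainty into the Monte Carlo simulations.

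Under either method, use day-0 costs and utility only as baseline covariates, never as a source for trial-period costs. Add one sensitivity analysis under a missing-not-at-random assumption, for example lower utility after withdrawal. State the recall period of the cost questionnaires, so that the period each one covers is clear.

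The cost is revised wording and modest extra analysis work. No new data are needed.

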#### **8.4 Interim analysis (if applicable)**

**Not applicable**

### **9. ETHICAL CONSIDERATIONS**

#### **9.1 Regulation statement**

The study will be conducted according to the principles of the Declaration of Helsinki (version October 2008) and in accordance with the Medical Research Involving Human Subjects Act (WMO).

#### **9.2 Recruitment and consent**

Participants will be guaranteed privacy, anonymity, and confidentiality, and will be told explicitly that they are allowed to withdraw from the study at any time. Furthermore, they will be informed that the researchers have the right to exclude them from participation at any time. The information will be given to participants in the form of a written patient information brochure containing also the informed consent form. At least 24 hours after receiving this information, potential participants will be contacted again by telephone. This will give the potential participant time to reflect on the study and the implications of consent. Any remaining questions of the potential participant will be answered and the researcher will perform a first exclusion screening based on the pre-screening questionnaire that is part of the information brochure. If there is no reason to exclude the potential participant based on these questions, the appointment will be made. Before inclusion, all participants are required to sign the informed consent form.

#### **9.3 Objection by minors or incapacitated subjects (if applicable)**

**Not applicable**

#### **9.4 Benefits and risks assessment, group relatedness**

**Not applicable**

#### **9.5 Compensation for injury**

The sponsor/investigator has a liability insurance which is in accordance with article 7 of the WMO.

The sponsor (also) has an insurance which is in accordance with the legal requirements in the Netherlands ((Article 7 WMO and the Measure regarding Compulsory Insurance for

Clinical Research in Humans of 23th June 2015). This insurance provides cover for damage to research subjects through injury or death caused by the study.

For details of these insurances we refer to the appendices G2 and G1 respectively.

### **9.6 Incentives (if applicable)**

As our study is executed in the context of common clinical practice, patients will not be offered specific incentives.

## **ADMINISTRATIVE ASPECTS, MONITORING AND PUBLICATION**

### **9.7 Handling and storage of data and documents**

The investigator will ensure that the subject's anonymity will be maintained. On all documents subjects will be identified only by an identification code – not by their names or hospital/clinical number. The investigator will keep a separate Subject Identification Code List, which matches identifying codes with the subject's names. Documents will be maintained by the investigator in strict confidence. Subject anonymity has to maintain upon all archiving steps. After cessation of the whole study (finalized and signed research report) the investigator will store the investigator file and copies of the CRFs to fulfill his responsibility to maintain adequate human study records for at least 2 years after the final publication or longer if required by the applicable legislation. Handling of personal data will comply with the Dutch Personal Data Protection Act. Subjects will be given a personal identification number, based on a random number generator. The executive investigator only will have the key to the code and will be able to track back data to personal subjects. Personal data will be kept separately from the experimental data acquired.

All biological materials will be coded on the patient's identification number and stored at the department of Human genetics Radboudumc according to the department's storage procedures. Only [name] and [name] will have access to the key of the code. All materials will be stored for 25 years. After this period and in case of withdrawal of the patients (on their request) the materials will be destroyed. Aim of storage is to be able to perform additional analyses. If analyses are suggested which are beyond the scope of the current informed consent we will request for additional permission at the CMO (amendment to the current protocol) and we will approach the patients for a separate written consent. **The CMO will also be consulted before genetic analyses will performed which include a risk of incidental findings**

Biomaterials will not be released unless there is a separate permission by the CMO (permission after request).

### **9.8 Monitoring and Quality Assurance**

Before the start of the study a monitoring plan will be developed under the supervision of the clinical research centre Nijmegen.

Monitoring will be performed in this study by a GCP certified monitor. Prior to first screening an initiation visit will be performed with the site (CRCN) and after the trial a close out visit will be performed with each study site.

The monitoring will consists of:

- check essential documents at the site
- check eligibility of subjects prior to study start
- monitoring for completeness and correctness of the source documents
- monitoring of the data in the CRCN workbook, and transfer of data from source documents to the eCRF (database management system CASTOR).

Checklists will be used containing the most important instructions.

### **9.9 Annual progress report**

The sponsor/investigator will submit a summary of the progress of the trial to the accredited METC once a year. Information will be provided on the date of inclusion of the first subject, numbers of subjects included and numbers of subjects that have completed the trial, serious adverse events/ serious adverse reactions, other problems, and amendments.

### **9.10 Temporary halt and (prematurely) end of study report**

The investigator/sponsor will notify the accredited METC of the end of the study within a period of 8 weeks. The end of the study is defined as the last patient's last visit.

The sponsor will notify the METC immediately of a temporary halt of the study, including the reason of such an action.

In case the study is ended prematurely, the sponsor will notify the accredited METC within 15 days, including the reasons for the premature termination.

Within one year after the end of the study, the investigator/sponsor will submit a final study report with the results of the study, including any publications/abstracts of the study, to the accredited METC.

## 10. Public disclosure and publication policy

The study will be registered at <https://clinicaltrials.gov>

The results will be published in international scientific peer reviewed journals.

The public disclosure and publication of the research data will be in agreement with the guidelines of ZonMW. Below we present our strategies in more detail.

To achieve implementation the results of our study must quickly find their way to clinicians, clinical genetic physicians and pharmacists and patients. In a collaborative, interdisciplinary effort we aim to submit our results to national and international peer reviewed journals and present them on national and international congresses, public and patient symposia and workshops.

We expect that our study results will be used to inform treatment recommendations as expressed in future clinical guidelines. This will be facilitated by the national and international positions held by our team members and advisors (among others): [name] chairs the Dutch Psychiatric Association (NVvP) workgroup preparing the guidelines for pharmacogenetics based dosing and Therapeutic Drug Monitoring. [name] chairs the Dutch Program for Quality Networks, coordinating the development of all National Guidelines in Mental Health. [name] chairs the “Zorgstandaard Depressie” (National Depression Guideline) and is editor of the Dutch and Flemish Journal of Psychiatry (Tijdschrift voor Psychiatrie). [name] and [name] are members of the Pharmacogenetics workgroup of the KNMP. Drs. [name], [name] and [name] are board members of the Dutch Clinical Pharmacogenetics Network. [name] is the President of the European Society for Pharmacogenomics & Personalised Therapy (ESPT). [name] is the chairman of the Dutch Society for Clinical Pharmacology and the President-Elect of the International Society for Therapeutic Drug Monitoring and Clinical Toxicology.

All investigators have extensive experience in publication in national and international peer reviewed journals and take actively part in the local, regional and national education programmes for psychiatrists, clinical genetics physicians, pharmacists, general medical doctors and other health professionals.

## 11. STRUCTURED RISK ANALYSIS

Potential issues of concern. The only extra risk participants are exposed to is the risk associated with the extra venepunctures. The aim of the study is to decrease the risk associated with CYP450 unadjusted prescription of TCA's. In the intervention group we therefore expect lower chances for side effects and a reduced time to therapeutic response compared to treatment as usual. The weekly monitoring for side effects and depressive symptoms in all participating patients give a low burden to the patients but contribute to extra safety compared to regular care.

Because the only risk is determined by the venepunctures the items below are not applicable.

